### Interim analyses {21b}

The data monitoring committee will act in an advisory role to ensure safety by reviewing the cumulative data from the clinical trial. An interim analysis will be performed once 50% of the sample has been achieved. The effects of the study will be assessed on clinical outcomes. The sample size of the study will increase, if necessary, based on the interim analysis. The monitoring committee may recommend modifying or terminating a clinical trial based on any perceived safety concerns, regardless of statistical significance. The sponsor is authorized to stop the study at any time if the safety of the participants is compromised.

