### Sample size {14}

According to previous studies tracking HALT of bioprosthetic heart valves, the rate has been estimated to be up to 39% [4, 7–9] among surgical valves. It has been estimated that there might be a 60–70% decrease in the incidence of HALT of bioprosthetic valves among patients receiving oral anticoagulants when compared to antiplatelet therapy [21]. If it is to be expected that HALT of the biological valve in the study will occur in about 30% of control patients, a premise of a 60% decrease in the prevalence after a 3-month treatment period seems reasonable and relevant. The null hypothesis is that compared to the ASA controls, apixaban treatment will not mitigate HALT prevalence among patients after rapid deployment AVR following a 3-month treatment period. With 158 participants randomized 1:1, we expect to have 80% power (type I error < 0.2) to detect a significant difference (type I error < 0.05) between the study groups, thus rejecting the null hypothesis. To account for protocol violation, loss to follow-up, and withdrawal of consent in 5% of participants, we aim to randomize at least 166 patients.

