## Statistical methods

### Statistical methods for primary and secondary outcomes {20a}

The primary outcome will be tested using the chi-square test of proportions. It will be tested for superiority using a 2-sided chi-square test at the 0.05 significance level in the intention-to-treat population. The secondary outcome will be test for non-inferiority with a single comparison between the study groups of the secondary outcome measure (safety composite) per-protocol. To test for noninferiority, we determined whether the upper boundary of the 95% confidence interval for the difference in the rate of secondary outcome measure between the treatment group and the control group was less than or equal to the prespecified noninferiority margin of 5 percentage points. If this requirement for noninferiority will be met, testing for the superiority of the safety composite will be performed at a two-sided alpha level of 0.05. The Kolmogorov-Smirnov test will be used to test normality of distribution for continuous data. For exploratory outcome measures, between-group differences will be analyzed using independent samples *t*-tests, chi-square test, or Mann-Whitney tests, where appropriate. If necessary, multivariable regression analysis will be used to adjust for imbalances in main prognostic variables between the intervention and control groups. Time-to-event analysis for the safety composite outcome and its components will be performed. Cumulative event-free survival will be estimated by Kaplan-Meier analysis.

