### Composition of the data monitoring committee, its role and reporting structure {21a}

An independent data safety monitoring board, consisting of a specialist cardiac surgeon and an independent trial statistician, is responsible for monitoring safety during the trial. An independent trial statistician will perform the statistical analyses. No formal stopping criteria are defined; the data safety monitoring board will give recommendations of stopping the trial if they consider interim data to be convincing.

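### The interim look permits stopping on undefined grounds and an unruled sample-size increase, while every final test stays at the full 0.05, so the stated type I error is not guaranteed

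*Protocol article*

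**What the plan says.** **Interim analyses {21b}** plans one analysis once half the sample has been reached. It says "The effects of the study will be assessed on clinical outcomes" and then "The sample size of the study will increase, if necessary, based on the interim analysis". No rule, cap or test procedure accompanies the increase. The same section lets the committee recommend modification or termination on any perceived safety concern.

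**Composition of the data monitoring committee {21a}** states outright that no formal stopping criteria are defined, and adds that "the data safety monitoring board will give recommendations of stopping the trial if they consider interim data to be convincing". Convincing is not restricted to harm.

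**Exploratory objectives** lists the clinical outcomes as stroke, myocardial infarction, reoperation and mortality. HALT is not among them.

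**Statistical methods {20a}** says of the primary outcome: "It will be tested for superiority using a 2-sided chi-square test at the 0.05 significance level in the intention-to-treat population". The safety composite is tested for non-inferiority with an ordinary 95% confidence interval against a 5-point margin, then for superiority at two-sided 0.05. None of the three is adjusted for the interim.

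**Sample size {14}** rests on HALT alone: the premise is that "HALT of the biological valve in the study will occur in about 30% of control patients", with a 60% relative reduction.

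**The concern.** A level of 0.05 is held by a final test at 0.05 only if the data had one chance to produce a positive claim and the amount of data was not chosen by looking at the tested effect. The plan leaves both conditions open. It does not say which outcomes are compared by arm at the interim, what would count as convincing, or what would trigger an increase.

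A second weakness concerns purpose. The number of patients was fixed by an assumed HALT rate, yet the only sample-size review is tied to clinical outcomes, which do not show whether that rate holds. It could enlarge the trial for an unrelated reason and miss a shortfall in HALT events.

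**Working it through.** **Inputs.** Two-sided alpha 0.05 (Statistical methods {20a}, Sample size {14}); 158 evaluable, 79 per arm; HALT 30% versus 0.4 × 30% = 12%; one look at half the information ({21b}). The interim thresholds and the size of any increase are my assumptions, because none is given.

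**1. The plan's own figure.** The claim is "With 158 participants randomized 1:1, we expect to have 80% power". With pooled rate (0.30 + 0.12)/2 = 0.21:

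n per arm = [1.960·√(2·0.21·0.79) + 0.842·√(0.30·0.70 + 0.12·0.88)]² / 0.18² = (1.960·0.576 + 0.842·0.562)² / 0.0324 = 79.2

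This rounds up to 80 per arm, 160 in total. At 79 per arm the power is Φ[(0.18 − 1.960·0.0648)/0.0632] = Φ(0.838) = 79.9%. The figure reproduces, as a fixed design with a single test and no allowance for an interim look.

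**2. Reading A: HALT is compared by arm and the trial may stop for benefit.** The two test statistics have correlation √0.5 = 0.707. Overall error = 1 − P(|Z₁| < c₁ and |Z₂| < 1.960).

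| Assumed interim stop | c₁ | Overall error, final test at 0.05 |
|---|---|---|
| p < 0.001 | 3.291 | 5.02% |
| p < 0.005 | 2.807 | 5.2% |
| p < 0.01 | 2.576 | 5.5% |
| p < 0.05 | 1.960 | 8.3% |

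**3. An increase steered by the interim effect on the tested outcome.** Let the second stage be r times the first (r = 1 is the original plan). The ordinary final statistic is Z = (Z₁ + √r·Z₂′)/√(1 + r), where Z₂′ is the second-stage statistic. For each interim value, take the r that maximises the chance that |Z| exceeds 1.960, then average over Z₁ under the null:

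- second stage up to doubled (total up to 1.5 times): 5.8%
- second stage up to tripled (total up to 2 times): 6.2%

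If the increase is decided on an outcome independent of the tested one, simulation gives 5.0%: no inflation.

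**4. Reading B: only clinical outcomes are seen.** If these are independent of HALT, the last line of step 3 applies and the HALT test stays at about 5%. The safety composite is different. It shares stroke, myocardial infarction and death with the listed clinical outcomes, so an increase can follow its interim effect. The worst case for its superiority test is 5.8–6.2%. The non-inferiority test uses only the upper bound of a 95% interval, a one-sided 2.5% test; by symmetry its worst case is 5.8/2 = 2.9% to 6.2/2 = 3.1%. These are upper limits. The composite also contains bleeding, which the list of clinical outcomes omits, so the steering would be imperfect.

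**5. What a review of clinical outcomes cannot see.** With 79 per arm and the 60% reduction kept, the formula in step 1 gives:

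| Control HALT rate | Power |
|---|---|
| 30% | 79.9% |
| 25% | 70.2% |
| 20% | 58.6% |
| 15% | 45.4% |

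The Background reports 5–39% after surgical replacement and no study of HALT in rapid deployment valves, and the primary outcome counts only grade 3 or higher. The 30% could therefore miss in a way that matters.

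**The case against.** The best defence is that the board is there for safety. Section {21a} gives it responsibility for monitoring safety, {21b} calls its role advisory and ties termination to safety concerns, and the effects assessed are clinical ones. Stopping for harm does not raise the chance of a false efficacy claim. The imaging assessors also stay blinded until the analysis is done. The statistical analysis plan mentioned under blinding is not shown and may hold the re-estimation rule.

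Much of this stands. A reader might infer that the trial's false-positive rate is 8.3%. The documents do not support that: the figure needs a by-arm HALT comparison and a stop for benefit at p<0.05, and neither is stated. A reader might also infer that an increase driven by clinical outcomes inflates the HALT test. It does not, if those outcomes are independent of HALT, so the 5.8–6.2% should not be attached to the primary test on that reading.

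The defence does not close the gap. The article does not merely leave stopping criteria to another document; it says there are none. Its wording on convincing data is not confined to harm, and safety stopping is already covered separately. The safety-focused reading is also the one that exposes the safety composite.

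**Conclusion.** The concern holds in a limited form: the stated 0.05 is not guaranteed, which is less than saying it is breached.

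- If HALT is compared by arm with a possible stop for benefit, overall error is 5.02% to 8.3%, depending wholly on an unstated threshold.
- If only clinical outcomes are seen, the HALT test is safe at about 5% (assuming independence). The safety-composite tests are exposed, at most to about 5.8–6.2% two-sided under the assumed limits on the increase, and the review cannot check the HALT rate behind the sample size.

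Either way something is unprotected, and the text does not say which case applies. This is not a claim that the 80% power is wrong or overstated: it reproduces, and Sample size {14} already makes it conditional on 30%.

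**What to change.** In {21b} and {21a}, with matching wording in {20a}, before any interim data are seen:

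1. State whether HALT is compared by arm at the interim.
2. Allow no early stop for efficacy, or only one at a strict boundary. Haybittle-Peto at p<0.001 leaves the final test at about 0.05 (overall 5.02%). O'Brien-Fleming uses 0.0052 at the interim and 0.0480 at the end; it needs about 162 evaluable patients, or gives 79.4% power at 158. Leave safety stopping to the board's discretion.
3. Base any sample-size increase on the blinded pooled HALT rate, with a stated cap. The expected value is (30% + 12%)/2 = 21%. If between-arm data are used instead, apply a combination or conditional-error test to the affected outcome, including the safety composite.

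The cost is mostly wording. The informal early efficacy stop is given up. A blinded pooled rate also cannot separate a low control rate from a large effect: 15% versus 6% and 19% versus 2% both pool to 10.5%. The increase rule should acknowledge this.

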### Methods for additional analyses (e.g., subgroup analyses) {20b}

Not applicable. No plans for additional analyses.

### Methods in analysis to handle protocol non-adherence and any statistical methods to handle missing data {20c}

Study population will be randomized to the intervention (apixaban) or the control (ASA) arm. Carefully selected patients based on the inclusion/exclusion criteria will provide a basis for a steady protocol adherence. In 5% of patients, a protocol violation, loss to follow-up, and withdrawal of consent are anticipated. All patients will remain in their originally allocated arm for the intention-to-treat analysis of all outcomes. Exploratory analyses will include a per-protocol analysis, which will include only patients who received their randomly assigned treatment, and an as-treated analysis in which we will compare patients who received apixaban with those who received aspirin with multivariable adjustment for imbalances in baseline characteristics. Maximal efforts to reduce the missing data to a minimum will be employed. Missing data will be handled via multiple imputations in statistical analyses.

### Plans to give access to the full protocol, participant-level data, and statistical code {31c}

The datasets analyzed during the current study are available from the corresponding author upon a valid request.

## Oversight and monitoring

### Composition of the coordinating center and trial steering committee {5d}

The overall responsibility for the study and its management will be with the PI. The trial steering committee is comprised of senior members of the Department of Cardiac Surgery at the University Hospital Center Zagreb. The steering committee will be responsible for the day-to-day running of the trial.

### Composition of the data monitoring committee, its role and reporting structure {21a}

An independent data safety monitoring board, consisting of a specialist cardiac surgeon and an independent trial statistician, is responsible for monitoring safety during the trial. An independent trial statistician will perform the statistical analyses. No formal stopping criteria are defined; the data safety monitoring board will give recommendations of stopping the trial if they consider interim data to be convincing.

### Adverse event reporting and harms {22}

During the entire study adverse event and any unintended effect of trial interventions will be collected. Participants will be asked to report any adverse event that they might have experienced after starting the study drug. They will also be able to contact the PI via the phone number listed in the informed consent form at any time to report any clinical or adverse event. Adverse events that may cause the subject to terminate protocol treatment are bleeding events. Thromboembolic events or bioprosthetic valve dysfunction might lead to crossover. We have clearly described adverse events we are planning to collect for outcome analysis. They will be labeled in primary or secondary outcomes. These outcomes will be reported in case report forms and do not need to be reported separately.

### Frequency and plans for auditing trial conduct {23}

Although this is a low-risk intervention trial, the trial steering committee and the independent safety monitoring board will meet 4 times a year to review the conduct throughout the trial period. The Institutional Review Board has the right to audit studies.

### Plans for communicating important protocol amendments to relevant parties (e.g., trial participants, ethical committees) {25}

Protocol amendments will be submitted to the appropriate ethics committee for approval before implementation. All agreed protocol amendments will be clearly recorded on a protocol amendment form and will be signed and dated by the original protocol approving signatories. As soon as approved, the PI will notify the trial participants and the sponsor. A copy of the revised protocol will be archived in file. Any deviations from the protocol will be fully documented using a breach report form. In case of protocol amendments, they will be updated in the clinical trial registry as well.

### Dissemination plans {31a}

De-identified patient data can be made available after the study-specific aims have been published. The statistical analyses will be available for those who request it based on published analyses. Authorship of the final report will be based on contribution to the trial as determined by the PI. The final report will be published in a peer-reviewed journal. Should the study participants indicate an interest in receiving these results, they will be shared with them.

## Discussion

Valve thrombosis is a common cause of prosthetic valve dysfunction. It may be related to inadequate antithrombotic therapy. Bioprosthetic valve thrombosis is a major cause of either acute or indolent bioprosthetic valve degeneration and often has an elusive presentation causing delayed recognition and treatment.

Subclinical leaflet thrombosis is found with significant frequency among bioprosthetic valves. It is characterized by HALT and RLM on high-resolution 4-dimensional cardiac CT. While the occurrence of HALT has been described across several transcatheter and surgical bioprostheses [5, 21], its effect on long-term valve function remains unclear [4, 7]. One of the reasons for the unclear relationship between HALT and long-term valve function might be related to the natural history of subclinical leaflet thrombosis. It is possible that HALT may exhibit spontaneous progression or even regression as part of its natural history, regardless of pharmacotherapy [23]. Whether more aggressive antithrombotic strategies could mitigate the occurrence of subclinical leaflet thrombosis is a matter of ongoing debate. Recent guidelines recommend a selective use of oral anticoagulants in patients with confirmed HALT and RLM with elevated gradients (Class of recommendation IIa, Level of evidence B) [10].

Over the last two decades, minimally invasive cardiac surgery has been developing rapidly [24]. Alongside the development of minimally invasive cardiac surgery, new sutureless and rapid deployment bioprosthetic valves were developed. They were developed to reduce ischemic times by avoiding the use of sutures to fix the valve to the annulus because of a new stent configuration, which can expand and thus anchor the valve in the right position [25]. These valves are conceptually different from the conventional bioprosthetic valves that require suture anchoring for the aortic annulus. It has been suggested that the stent frame and leaflets design of rapid deployment and sutureless valves may have a potential influence of thrombus formation and, hence, risk of stroke [9]. Current knowledge about antithrombotic treatment of patients implanted with this novel biological prosthesis is very limited and is not based on randomized studies. Moreover, antithrombotic recommendations in the guidelines are lacking as well.

This is the first trial of its kind to investigate the efficacy of apixaban in the prevention of latent bioprosthetic valve thrombosis after AVR with new generation rapid deployment bioprostheses. The proposed study addresses an unanswered question regarding the prevention of silent valve thrombosis after bioprosthetic valve implantation. Direct oral anticoagulants have not been studied for antithrombotic treatment in the early postoperative period.

There are two statistical concerns with the trial. First, this is a single-center study that may limit its external validity, the results may not be generalizable to other populations or settings, and there may be variations in practice and patient characteristics that could affect the outcomes. Second, this study has limited statistical power. To overcome these issues, we will employ efforts to expand the study to multiple regional centers. Apixaban has the theoretical potential to improve subclinical biological valve thrombosis and maintain low risk of bleeding. If shown to be effective, this trial may serve to change the way of antithrombotic management after AVR, paving the way for further research.

## Trial status

This manuscript was based on protocol version 1.2, dated March 3, 2023. Recruitment for this study began in December 2023 and it is expected to be completed by the end of 2025.

## Data Availability

Any data required to support the protocol will be supplied upon reasonable request if all members of the investigative team approve the request.

## Abbreviations

ASA: Acetylsalicylic acid
AVR: Aortic valve replacement
CT: Computed tomography
HALT: Hypo-attenuated leaflet thickening
DOAC: Direct oral anticoagulant
EOA: Effective orifice area
NYHA: New York Heart Association
PI: Principal investigator
RLM: Reduced leaflet motion
TAVI: Transcatheter aortic valve implantation
TEE: Transesophageal echocardiography
TTE: Transthoracic echocardiography
VARC: Valve Academic Research Consortium
VKA: Vitamin K antagonists
